## Abstract

**Abstract:**

**Purpose:**

Interestingly, 30–50% of patients undergoing elective cardiothoracic surgery develop postoperative AF (PoAF). Unfortunately, preventive PoAF therapy is still suboptimal. In our previous studies, we showed that oral Geranylgeranylacetone (GGA) administration increased cardioprotective heat shock protein (HSP) protecting against AF onset and progression in clinically relevant animal model studies.

**Methods:**

The GENIALITY study is a phase II single-center, double-blind, placebo-controlled randomized trial comparing the efficacy of GGA in preventing PoAF. Participants (*N* = 146) are adult patients, without any registered history of AF, undergoing elective open-heart surgery for valvular disease, coronary artery bypass grafting, or concomitant, and are allocated with ratio 1:1 in treatment or placebo groups. Daily administration of 300 mg of GGA or placebo starts 5 days before until 3 days after surgery. Cardiac rhythm will be monitored using a Holter monitoring post-surgery until hospital discharge. Additionally, blood samples, right atrial appendage tissue, and epicardial adipose tissue will be collected to assess proteostasis levels.

**Results:**

The primary endpoint is the assessment of PoAF incidence in the GGA group compared to the placebo group. Secondary endpoints include the evaluation of HSP levels through biochemical analysis in both blood and atrial tissue.

**Conclusion:**

The GENIALITY study aims to reduce PoAF incidence in the GGA group compared to the placebo group. Herewith, we expect to obtain proof of concept for a beneficial effect of GGA in preventing PoAF in patients undergoing cardiothoracic surgery.

**Trial Registration:**

Clinical Trial Information System (CTIS) registry: 2024–514743-28–00. Authorized on September 30th 2024.

## Introduction

Atrial fibrillation (AF) is the most common cardiac arrhythmia in Western countries, with a predicted prevalence of nearly 18 million diagnosed patients in 2060 [1]. AF is a progressive disease associated with an increased risk of stroke, heart failure, and mortality [2]. AF progression is rooted in the combination of structural and electrical atrial remodeling [3].

Postoperative AF (PoAF) is defined as new-onset AF in the immediate period following cardiothoracic surgery and is the most common complication following cardiac surgeries [4, 5]. The incidence of PoAF ranges between 30 and 50% in patients undergoing cardiac surgical procedures [4, 6]. Common characteristics involve an onset occurring 2–4 days after surgery [4], with episodes that are typically brief and self-terminating. Associated clinical and epidemiological consequences of PoAF include increased risk of stroke, hemodynamic instability, lengthened hospital and intensive care unit stays, and higher (or increased) health-care costs [1]. Although the European Society of Cardiology recommends prophylactic use of ß-blockers for patients at risk of PoAF [1], there is still a lack of consistent data from large randomized clinical trials supporting the efficacy of such medications in reducing the incidence of PoAF. This underscores the urgent need to identify effective drugs for PoAF prevention. Moreover, reason for suboptimal treatment is that the underlying mechanisms for PoAF are incompletely understood. Potential pathophysiological mechanisms involved include inflammation, sympathetic activation, and cardiac ischemia. These factors collectively may trigger PoAF, especially in parallel to pre-existing factors, including atrial electropathology that render the atria susceptible to AF onset and progression [7].

Emerging research findings reveal a key role for protein homeostasis (proteostasis) derailment to drive AF. A balanced proteostasis is of vital importance for the proper function of cardiomyocytes and the heart overall [3, 8]. Given the limited regenerative capacity in long-lived postmitotic cardiomyocytes, proteostasis plays a role of paramount significance to maintain a healthy heart function. During stress, including cardiac surgery, cardiomyocytes respond by inducing a heat shock response (HSR), by activating heat shock protein (HSP) expression. HSPs are chaperones capable of binding to proteins such as cytoskeletal and sarcomere protein structures and thereby preventing them from misfolding and disruption and as such protect against electropathology and AF onset and progression [9–13]. Previous research findings disclosed that especially small HSPs bind to myofibrils and protect against myofibril degradation in experimental and clinical AF [9, 11, 14]. Clinical studies show that the higher expression of HSPB1 in atrial tissue samples was associated with short duration of AF and with minimal degradation of sarcomere protein structures [9, 10, 15]. In line, research showed that the derailment of the HSR and exhaustion of atrial HSP levels play an important role underlying electropathology and AF progression [9, 10, 16].

Hence these molecular mechanistic insights pave importance to HSR boosting as a novel pharmacological strategy to reduce AF risk. The HSP-inducing compound geranylgeranylacetone (GGA) may present as a suitable candidate. GGA likely confers its cardioprotective effects on AF, by enhancing HSF1 hyperphosphorylation with the subsequent induction of cardioprotective HSP expression [15]. The cardioprotective effect of GGA is likely via the increased expression of HSPB1, as ablation of this HSP diminishes the protective effect of GGA [10, 15]. HSPB1 binds to structural proteins and as such conserves the cardiomyocyte structure and function [8, 10, 14]. In addition, GGA enhances protein and functional recovery in an in vitro model for AF [11]. The small signaling protein RhoA appears to be engaged in this mechanism, mediated by C20 (geranylgeranyl) isoprenoids via its post-translational prenylation [17]. GGA may compete with endogenous geranyl groups affecting RhoA activation and consequently enhancing HSP expression. Interestingly, previous research raised importance of the geranyl group within the GGA structure, given that a loss of HSP induction was observed in the administration of GGA derivates with farnesyl isoprenoid (C15) [15].

Additionally, GGA has been shown to enhance cardiomyocyte HSP expression levels. In an in vitro AF atrial cardiomyocyte model system, the administration of GGA boosted HSP expression and protected against contractile dysfunction [14]. In a *Drosophila* AF model, GGA protected against myocardial dysfunction and increased arrhythmicity [14]. The administration of GGA in dog models for rapid-pacing and acute ischemia-induced AF protected the heart against electrophysiological impairment, contractile dysfunction, and AF onset and progression [9, 18]. Furthermore, protective effects of HSPs against AF inducibility were observed in a rabbit heart failure model system [19]. Importantly, a placebo-controlled clinical trial in patients with coronary artery disease, administering orally 400 mg/day of GGA for 3 days prior to coronary artery bypass grafting surgery, already resulted in a significant increase in HSP expression in the right and left atrial appendages compared to placebo-treated patients. Moreover, increased HSP levels, especially HSPB1, were present at the myofilaments in patients treated with GGA, suggesting a beneficial effect by the conservation of the myofilament structures [14].

Based on the observed cardioprotective findings of GGA, in the current phase II trial, we aim to test a beneficial effect of GGA in preventing PoAF in patients undergoing cardiothoracic surgery.

## Study Design

The GENIALITY study is a prospective interventional trial, with a scheduled duration of 18 months. After eligibility is checked and informed consent (IC) is obtained, patients are invited for a baseline visit 1 week before scheduled cardiothoracic surgery. During this visit, a physical examination and blood collection are performed, and instructions about treatment/placebo administration are provided. Five days before and until 3 days after cardiothoracic surgery, participants are instructed to start 2 mL/day of treatment administration, either placebo (2 mL Miglyol 812 N) or GGA solution (300 mg GGA in 2 mL of Miglyol 812 N). Although the standard “on-label” dosage for the treatment of stomach ulcers and gastritis is 150 mg/day [20], a higher dosage of 300 mg/day was safe for participants in other clinical trials [21, 22] and is closer to the dose of 400 mg/day for 3 days chosen by van Marion et al. [14]. Immediately before the commencement of cardiac surgery, a new blood sample is collected, which is processed into serum and stored at − 80 °C. Atrial tissue samples, collected from the right atrial appendage at the cannulation incision for extracorporeal circulation, and epicardial adipose tissue are immediately snap-frozen in liquid nitrogen and stored at − 80 °C. Immediately after surgery, the patient’s heart rhythm is continuously monitored by the Holter device until hospital discharge—usually on the third day post-surgery—or until the end of the 7th day post-surgery. Holter data are collected for further analysis by research staff to identify the incidence of PoAF longer than 10 s. While previous consensus statements defined sustained AF as lasting longer than 30 s [1], recent discussions emphasize the importance of reconsidering shorter thresholds in the context of continuous rhythm monitoring technology available today [23, 24]. After the last day of treatment/placebo administration, the third blood sample is collected. Three weeks after surgery, patients are contacted by phone for a follow-up appointment. Per patient, the protocol is depicted in Fig. 1. At the time of publication, the study is in the active enrollment phase.

**Fig. 1 Fig1:**
[figure not shown]
Study timeline

The study is carried out in adherence to the Declaration of Helsinki and in accordance with the Medical Research involving Human Subjects Act. Also, approval was granted by the local medical ethical committee of the Amsterdam University Medical Centra with the number MEC 2024.1014, recorded in the Clinical Trial Information System (CTIS) registry with the trial number 2024–514743-28-00.

### Study Objectives

The primary objectives are to evaluate whether GGA administration reduces the incidence of PoAF in patients undergoing open-chest cardiac surgery compared to a placebo. The secondary objective is to investigate the activation of the HSR by measuring HSP levels after GGA treatment compared to a placebo in blood and atrial adipose and myocardial tissue samples.

### Study Population

The study population (*N* = 146) consists of adults (18–80 years old) who never had documented history of AF. Patients who are diagnosed with mitral valve stenosis or regurgitation, and/or aortic valve stenosis or regurgitation, and/or coronary artery disease are scheduled for valve repair/replacement and/or coronary artery bypass grafting (CABG) at Amsterdam UMC.

### Inclusion Criteria

In order to be eligible to participate in this study, a subject must meet all of the following criteria:Aged between 18 and 80 years old.Elected for cardiothoracic surgery for mitral valve stenosis or regurgitation, and/or aortic valve stenosis or regurgitation, and/or coronary artery disease

### Exclusion Criteria

A potential participant who meets any of the following criteria is excluded from participation in this study:Documented history of AFNot able to undergo the complete study protocolPrevious cardiothoracic surgeryDoubt about compliancePre-menopausal women who are nursing or pregnantChronic malabsorptionAny documented or suspected malignancy or history of malignancy within 1 year prior to screening, except appropriate treated basal cell carcinoma or in situ carcinoma of the cervixCurrently enrolled in another drug trial

### Sample Size Calculation

Based on our study population, the expected incidence of PoAF in our study population is 32% [25]. The sample size calculation of the present study design was based on dichotomous outcomes for two independent groups (treatment and placebo), as this parameter has an expected incidence drop from 32 to 12%, where alpha = 5%, beta = 0.2, and power = 80% and 2-sided testing [R Statistics 3.6.3, pwr-package 1.3–0]. Therefore, the initial required number of patients undergoing cardiac surgery is 66 in the GGA-treated group and 66 in the placebo group. An attrition rate of 10% increases this to 73 patients in the GGA-treated group and 73 in the placebo group.

### Continuous Heart Monitoring (Holter)

Immediately after cardiothoracic surgery, the heart rhythm of each patient is continuously monitored by a Holter until hospital discharge. In the case of post-operative hospitalization lasting longer than 7 days, Holter examination is discontinued by the end of the 7th day.

### Blood Sampling

During the baseline appointment, immediately before surgery, and on day 8 after the start of treatment/placebo, blood samples are collected and processed into serum, ultimately stored at − 80 °C.

### Atrial Tissue Sampling

During cardiothoracic surgery, after the introduction of the extra corporal circulation into the right atrium via the right atrial appendage (RAA), an atrial tissue sample (approximately 10 × 10 mm) is obtained from the incision site in all patients. Collected RAA samples are immediately snap-frozen in liquid nitrogen and stored at − 80 °C.

### Epicardial Adipose Tissue Sample

During cardiothoracic surgery, a small sample of epicardial adipose tissue (approximately 15 mg) is collected, which will be immediately snap-frozen in liquid nitrogen and stored at − 80 °C.

### Tissue Analysis

In order to study secondary objectives, serum samples, epicardial adipose, and atrial tissue samples are used to investigate the influence of GGA on HSPs levels, by assessing levels of HSPA1A, HSPB1, and phosphorylated HSF1, as well as the degree of structural remodeling using (confocal) microscopic imaging.

### Safety Laboratory Tests

In order to monitor the previously described liver enzymes’ elevation, from the first and last blood samples, the alkaline phosphatase, gamma-GT, ALT (alanine transaminase, SGPT), AST (aspartate transaminase, SGOT), and bilirubin total and fractionated are determined.

### Primary Endpoints

Holter data are used to identify the incidence of PoAF longer than 10 s.

### Secondary Endpoints

All collected tissue samples will be analyzed to assess levels of HSPB1, HSPA1A, and phosphorylated HSF1, and proteostasis markers, as well as the degree of structural remodeling using (confocal) microscopic imaging.

## Data Management

### Data Collection

Clinical data is collected and securely stored on an encrypted drive. Daily data transmitted via remote monitoring is downloaded from a password-protected cloud database. This data is preserved for 25 years after study completion. The data is used solely for the GENIALITY study, as detailed in the informed consent form.

### Confidentiality

Collected data is secured against unauthorized access. A unique study code is assigned to each participant. The study is conducted in compliance with the guidelines of Good Clinical Practice, in full conformance with the Declaration of Helsinki, and the law on Medical Research involving Human Subjects.

## Statistical Analyses

Regarding clinical characteristics from the study population, such as indication for cardiothoracic surgery, age, sex, BMI, hypertension, diabetes mellitus II, and statin intake, descriptive statistics of continuous variables will be presented as means with standard deviations (SD) or medians with interquartile ranges (IQR), depending on the distribution of the data. Categorical data will be presented as proportions and numbers.

The statistical efficacy analysis is conducted according to the intention-to-treat principle with a chi-square test for proportions of PoAF incidence until D3, between the treatment arms. All randomized patients are included in the primary endpoint analysis. We use the Cox-Mantel test in order to calculate survival rates (PoAF as outcome) until hospital discharge between treatment arms.

HSP levels are continuous measures assessed on adipose tissue and atrial tissue. Adipose and atrial tissue are collected once during surgery. Here, the comparison between control and intervention is cross-sectional, and individual measurements are independent. They will be analyzed using linear regression to compare study arms while adjusting for stratification factors (sex, age, and cardiac surgery indication). HSP levels are also continuous measures assessed on blood samples which are collected at three time points: baseline appointment, at day of surgery, and at day 3 after surgery (see Fig. 1). Therefore, we use statistics suited to longitudinal data, as these are thus dependent observations (correlated within patients). A linear mixed model with at least random intercepts, and, if required, random slopes for time and/or treatment, will be used to compare study arms while adjusting for stratification factors. To preserve the overall type I error rate over all secondary endpoints, Bonferroni correction will be used.

Values of *p* < 0.05 are considered statistically significant. SPSS version 20 (IBM Analytics), R Statistical Software (R Studio, Inc., Boston, MA, USA; version 1.0.153), and GraphPad Prism version 8.0 (GraphPad Software Inc., CA) are used for all statistical evaluations.

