### Randomisation and Blinding

For randomization, we consider a 1:1 allocation ratio. Stratified random sampling will take into consideration the following: age (18–60 years or 60–80 years old), sex (male and female), and indication for cardiothoracic surgery (valve disease, CABG, and concomitant valve disease + CABG). Therefore, 12 strata will be considered. A random block size of 4 will be considered.

Stabilization of atrial cardiomyocyte proteostasis appears to be an upcoming and promising therapeutic strategy to avert the AF onset. The GENIALITY trial is the first clinical study to investigate whether HSP-boosting therapy can clinically prevent the incidence of AF in patients undergoing cardiothoracic surgery. The study outcomes will also contribute to a better understanding of the HSP pathway under therapeutic intervention, fostering future investigations with GGA derivatives.

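### The primary PoAF chi-square ignores the factors that stratify randomisation; if they predict PoAF it stays valid but is mildly conservative and forgoes about 0 to 2 points of power

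*Protocol article*

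**What the plan says.** The article's Randomisation and Blinding section stratifies on "age (18–60 years or 60–80 years old), sex (male and female), and indication for cardiothoracic surgery". With two age bands, two sexes and three indications this makes 12 strata, with blocks of 4 and 1:1 allocation.

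In Statistical Analyses the primary test is given as "The statistical efficacy analysis is conducted according to the intention-to-treat principle with a chi-square test for proportions", comparing PoAF up to day 3 between arms. Time to PoAF until discharge is compared by a Cox-Mantel test. Neither comparison is described as stratified or adjusted.

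The same section treats the HSP measurements differently. For tissue levels: "They will be analyzed using linear regression to compare study arms while adjusting for stratification factors (sex, age, and cardiac surgery indication"). The mixed model for blood levels is adjusted for the same factors.

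Sample Size Calculation rests on an unadjusted comparison of two proportions: an "expected incidence drop from 32 to 12" per cent, "where alpha = 5%, beta = 0.2, and power = 80% and 2-sided testing", giving "66 in the GGA-treated group and 66 in the placebo group" before attrition.

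**The concern.** Stratified blocks force the arms to be nearly balanced on age band, sex and indication. Variation in PoAF risk between strata therefore largely drops out of the difference between arms. A plain chi-square does not know this and still counts that variation in its variance. When the factors predict the outcome, the test statistic is a little too small and the test rejects less often than 5% under the null.

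What is at stake is efficiency. The adjustment is planned for the mechanistic HSP endpoints, but not for the endpoint on which the trial is sized and judged. The factors are known for every randomised patient, so using them needs no new data.

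**Working it through.** **1. The plan's own figure.** Inputs from Sample Size Calculation: 32% vs 12%, two-sided alpha 0.05, power 80%.

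- Arcsine effect size: h = 2·asin(√0.32) − 2·asin(√0.12) = 0.495.
- n per arm = 2·[(1.960 + 0.842)/0.495]² = 64.05, so 65.
- The pooled-variance formula without continuity correction gives 67.

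The stated 66 lies between the two and is reproduced. Power at 66 per arm is 79.9% (pooled) or 81.2% (arcsine). At the 73 per arm to be randomised it is 83.8% (pooled).

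Expected events, averaging the two rates to (0.32 + 0.12)/2 = 0.22: 132 × 0.22 = 29 evaluable, or 146 × 0.22 = 32 if all randomised patients contribute.

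**2. How conservative the chi-square is.** Let stratum k have share w_k and null risk p_k, with overall risk p = 0.32, and let R² = Σ w_k(p_k − p)² / [p(1 − p)]. With full balance within strata, the variance of the arm difference is (1 − R²) times what the chi-square assumes. So true size ≈ 2Φ(−1.96/√(1 − R²)).

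The article gives neither stratum shares nor stratum risks. Assumed shares: 75% aged 60–80, 75% male, and 35/50/15% valve/CABG/both. Assumed odds ratios, in the order age, sex, valve, both (CABG as reference):

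- moderate: 2, 1.2, 1.5, 2.5
- strong: 3, 1.5, 2, 4
- very strong: 6, 2, 3, 8

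| Prognostic strength | R² | Size by formula | Simulated chi-square size |
|---|---|---|---|
| none | 0 | 5.0% | 5.05% |
| moderate | 0.041 | 2Φ(−2.001) = 4.5% | 4.6% |
| strong | 0.092 | 2Φ(−2.057) = 4.0% | 4.2% |
| very strong | 0.187 | 2Φ(−2.174) = 3.0% | 3.3% |

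The simulation used N = 132, 12 strata, blocks of 4 and 100,000 trials per case. Incomplete blocks leave some imbalance, which helps explain why the simulated sizes sit slightly above the formula.

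**3. Power forgone, 32% vs 12%, N = 132.** The comparators are a Cochran-Mantel-Haenszel (CMH) test over the 12 strata (100,000 runs) and a score test from a logistic model with main effects (20,000 runs).

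| Strength | Chi-square vs CMH | Difference | Chi-square vs score test | Difference | Score-test size |
|---|---|---|---|---|---|
| none | 81.0 vs 80.1% | −0.9 | 80.8 vs 81.5% | +0.7 | 5.4% |
| moderate | 81.2 vs 81.2% | 0 | 81.9 vs 83.4% | +1.5 | 5.4% |
| strong | 81.5 vs 82.8% | +1.3 | 81.7 vs 84.4% | +2.7 | 5.5% |
| very strong | 82.8 vs 86.2% | +3.4 | 82.8 vs 87.3% | +4.5 | 5.3% |

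CMH holds its size at about 5%. The score test does not: across all runs it sits at about 5.2 to 5.7%, so part of its apparent gain is extra alpha.

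**4. Removing the extra alpha.** A further set of 8,000 runs per case held the adjusted test to a true 5%. It used assumed odds ratios of 1.6, 2.0 and 2.5 per 10 years of age, with 2.0, 2.5 and 3.0 for indication. Adjusting for the factors as stratified gained about 0.5, 1.3 and 2.3 points over the chi-square. Using continuous age gained about 1.0, 2.0 and 3.9. The difference between these two rows comes from modelling age more finely, not from respecting the stratification.

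**5. Why main effects rather than 12 cells.** Under the assumed shares, five of the 12 cells are expected to hold fewer than 6 of 132 patients. The smallest is younger women having both procedures: 0.25 × 0.25 × 0.15 × 132 = 1.2. This sparsity is consistent with the roughly 1 point that the 12-cell CMH loses when the factors carry no information.

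**The case against.** The strongest defence is that nothing here is an error. The trial was sized for an unadjusted test at 80% power, the analysis uses that test, and its power was 80.8 to 82.8% in every case examined at N = 132. Its type I error stays at or below nominal, apart from simulation noise. A simple primary test is defensible with about 29 events, and an adjusted model with five terms (arm, age band, sex, two for indication) leaves 29/5 ≈ 6 events per term. All of this stands. It limits the point to efficiency that could be had at almost no cost.

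A reader might go further in four ways that the documents do not support:

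- **That the primary test is invalid or underpowered.** It is neither, under the plan's own assumptions.
- **That 2 to 4.5 points of power are being lost.** Gains of that size come from comparing with a test that runs above 5%, from replacing the age bands with continuous age, or from assuming very strong prognostic effects. Choosing the factors as stratifiers suggests that the sponsor thinks them relevant, but the article reports no PoAF rate by stratum.
- **That the Cox-Mantel test loses a known amount.** The same variance argument applies to an unstratified log-rank comparison, but no loss was calculated. An article may also leave stratification of that test to the analysis plan.
- **That a published interval would be too wide.** The article specifies no interval for the PoAF difference.

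**Conclusion.** The point holds as a minor-to-moderate, conditional efficiency loss in the primary test and an inconsistency with the adjusted HSP analyses. If age band, sex and indication are moderately to strongly prognostic, the chi-square's true size is about 4 to 4.6% and about 0 to 2 power points are forgone. Only very strong effects push size to about 3.3% and the loss above 3 points. If the factors are not prognostic, the choice makes essentially no difference.

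These sizes depend on assumed stratum shares and odds ratios, on N = 132, and on the planned 32% vs 12%. The mismatch between the stratified design and the unadjusted primary test is plain in the text and needs no assumption.

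**What to change.** Enrolment was still active at publication, so the change can be prespecified before unblinding:

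- Make the primary analysis a comparison adjusted for age band, sex and indication as main effects, not for all 12 cells. One option is logistic regression with the standardised risk difference and its 95% CI. If continuous age is preferred, justify it as a separate modelling choice.
- Choose a variance estimator or test whose type I error has been checked by simulation at about 29 to 32 events. Do not adopt the simple adjusted score test unchecked.
- Keep the unadjusted chi-square as a sensitivity analysis.
- For consistency, adjust or stratify the time-to-PoAF comparison for the same factors, without claiming a particular gain.

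The cost is protocol and analysis-plan wording, a small simulation and a few lines of code, with no extra patients or data. The downsides are about six events per model term and a slightly less simple primary test.

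### The tissue HSP regression could also adjust for the planned pre-treatment serum level of the same marker: an optional, near-free efficiency gain whose size depends on a correlation the protocol does not give

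*Protocol article*

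**What the plan says.** All references are to the protocol article.

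- **Tissue model (Statistical Analyses).** Atrial and adipose HSP levels come from one intra-operative sample per patient and are compared between arms by regression: "They will be analyzed using linear regression to compare study arms while adjusting for stratification factors (sex, age, and cardiac surgery indication". The list of covariates ends there. The section does not say whether levels are analysed as measured or after a transformation.
- **Serum timing (Study Design, Blood Sampling).** The baseline visit, with blood collection, is one week before surgery. Dosing starts five days before surgery. The sampling times are: "During the baseline appointment, immediately before surgery, and on day 8 after the start of treatment/placebo, blood samples are collected".
- **Same markers (Tissue Analysis).** "serum samples, epicardial adipose, and atrial tissue samples are used to investigate the influence of GGA on HSPs levels", with HSPA1A, HSPB1 and phosphorylated HSF1 listed for all three sample types.
- **Blood model (Statistical Analyses).** Serum levels go into a separate linear mixed model that includes the baseline time point.
- **Multiplicity (Statistical Analyses).** Bonferroni correction applies across the secondary endpoints. The number of tests is not given.
- **Sample size (Sample Size Calculation).** The trial is sized on postoperative AF only. No power, SD or target effect is given for HSP levels.

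**The concern.** HSP induction is the secondary objective and the mechanistic basis of the trial. The tissue comparison has no pre-treatment measure in its model, although one is already planned for each patient. The baseline serum level precedes the first dose, so treatment cannot affect it and it is a legitimate covariate. If it predicts the tissue level beyond sex, age and indication, including it removes residual variance and narrows the interval for the arm difference.

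This matters because the sample size was not set for this comparison and the significance threshold is reduced by Bonferroni. At stake is some power to detect true HSP induction in tissue. Bias, the type I error rate and the primary endpoint are not affected.

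**Working it through.** **1. The plan's own figure.** The only stated sample size is for postoperative AF: an "expected incidence drop from 32 to 12" per cent, "where alpha = 5%, beta = 0.2, and power = 80% and 2-sided testing", giving "66 in the GGA-treated group and 66 in the placebo group".
- Arcsine effect size: h = 2·asin(√0.32) − 2·asin(√0.12) = 0.495. Then n = 2 × ((1.960 + 0.842)/0.495)² ≈ 64.05, rounded up to 65 per arm.
- Pooled-variance formula: 67 per arm.
- The stated 66 lies between these, so it is reproduced.
- Attrition: 66 × 1.1 = 72.6, rounded up to the stated 73 (66/0.9 would give 74).

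This figure supplies the n used below but says nothing about power for HSP levels.

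**2. Inputs for the tissue comparison.**
- From the article: 66 analysed per arm, 1:1 allocation, and strata of sex (2 levels), age (2) and indication (3), which use 1 + 1 + 2 = 4 degrees of freedom.
- Assumed: effect of 0.5 SD, where SD is the residual SD given the strata; alpha = 0.05/9 (three markers × three sample types); correlation ρ between baseline serum and tissue level *after* the strata, from 0 to 0.5.

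**3. Formula.** Adding the covariate multiplies residual variance by (1 − ρ²).
- Noncentrality = 0.5/√(1 − ρ²) × √(66/2).
- Degrees of freedom = 132 − 2 − 4 = 126 without the covariate, 125 with it.
- Power = P(noncentral t > critical t), with critical t = 2.822 at two-sided 0.05/9.

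**4. Results at alpha 0.05/9.**

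| ρ | Residual variance | Noncentrality | Power |
|---|---|---|---|
| no covariate | 1.00 | 2.872 | 52.2% |
| 0 | 1.00 | 2.872 | 52.2% |
| 0.1 | 0.99 | 2.887 | 52.8% |
| 0.2 | 0.96 | 2.932 | 54.5% |
| 0.3 | 0.91 | 3.011 | 57.6% |
| 0.5 | 0.75 | 3.317 | 68.9% |

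A second degree of freedom, for a missingness indicator, changes none of these by more than 0.1 point.

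**5. Sensitivity to the number of tests.** With alpha = 0.05 (no division), the same formula gives 81.3% without the covariate, then 81.7%, 82.9%, 84.8% and 90.8% at ρ = 0.1, 0.2, 0.3 and 0.5. The pattern is the same: almost nothing below 0.2, a visible gain from about 0.3.

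**6. Simulation check.** This used 8,000 trials per setting, 66 per arm, alpha 0.05/9 and an effect set for nominal 80% power in the strata-only model, with chance imbalance between arms allowed.
- ρ = 0: 78.4% without the covariate, 78.3% with it.
- ρ = 0.1: 79.1% and 79.2%.
- ρ = 0.3: 78.3% and 82.8%.
- ρ = 0.5: 78.7% and 90.8%.

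The downside at ρ = 0 is negligible. The gain appears only once the correlation is appreciable.

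**The case against.** The case against runs as follows. The planned model is valid, adjusts for the randomisation strata, and cannot include a baseline tissue value because none exists. Serum is a different compartment from atrial or adipose tissue and is drawn about a week earlier. The article gives no serum-tissue correlation, and only the part not already explained by sex, age and indication counts. At 0.1 the gain is about half a point, and at 0.2 about two. Every input beyond the sample size and the strata is assumed, including the nine tests. Leaving out an optional covariate is a preference, not a mistake.

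Most of this stands, and it is why the point is put as an option. It does not remove the point altogether, because the article names its covariates explicitly, the candidate covariate is already being collected, and the trade is lopsided: almost no loss if the correlation is nil, and about 5 to 17 points in the table if it is 0.3 to 0.5.

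A reader might go further and infer that the regression is fitted to untransformed levels and loses power by not taking logs. The article does not support that. It states no analysis scale, and a condensed article may leave this to the analysis plan. Any advantage of logging would also rest on an assumed right-skewed distribution: for normal data with a coefficient of variation of 0.2 to 0.3, logging would cost about 1 to 5 points of power.

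**Conclusion.** The point holds as an optional efficiency gain on a secondary endpoint. The tissue regression lists only the stratification factors, and a pre-treatment serum level of the same marker is planned but not used in it. The planned analysis is neither biased nor invalid.

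The size is uncertain. The gain is negligible below a residual correlation of about 0.2 and material only from about 0.3. It would be wrong to conclude that the plan demonstrably forgoes power, since that depends on a correlation the document does not report. The power figures rest on the assumed 0.5 SD effect and nine Bonferroni tests. The ordering across correlations does not depend on the number of tests.

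**What to change.** In Statistical Analyses, extend the covariates of the tissue regression with: *and the baseline-visit serum level of the same marker, where measurable*. Add a simple rule for patients without a baseline value, for example mean imputation with a missingness indicator. Fix both before unblinding; the article reports that enrolment is still under way, so there is time.

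The cost is a sentence or two of wording and one or two of the 126 residual degrees of freedom. No new sample or assay is needed. If serum and tissue levels prove unrelated, the change brings no gain and essentially no loss.
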